## D Investigational Plan

### D1 Overview of Trial Design

PROMISE is a multicenter, randomized, pragmatic trial comparing 2 state-of-the-art diagnostic strategies in approximately 10,000 symptomatic, low-to-intermediate CAD-risk subjects with suspected CAD who require nonurgent testing. The following discussion includes trial assessments, outcomes, substudies, organization and operations, sites and site management, timeline, and potential criticisms. See the figure below for a schematic summary of the trial design.

[figure not shown]

### D2 Subject Population

To optimize the generalizability of the study results and reflect current patterns of care, subjects considered for enrollment into PROMISE will be outpatients without known CAD who are symptomatic, and whose physician has decided that the subject requires nonurgent, noninvasive cardiovascular testing to further evaluate suspected CAD. This population is purposefully and carefully chosen to be directly reflective of the population in which elective noninvasive cardiac diagnostic testing is currently being used.

PROMISE's inclusion criteria stipulate that all subjects will be symptomatic and will, in the judgment of the physician caring for the subject, require an elective noninvasive test

---

for symptoms suspicious for CAD. Thus, whether or not the subject chooses to participate in the trial, he or she will likely undergo testing. All of the modalities in PROMISE are clinically well established and performed routinely and safely across the U.S. No experimental treatment or testing is involved, and there should be equipoise about the feasibility to perform either functional OR anatomic testing. **The trial intervention is simply the random assignment of the initial test.**

### ***Justification of Population***

Since subjects are symptomatic and have already been determined to require outpatient noninvasive testing, this is an ideal population in which to compare the results of different testing strategies. We include subjects presenting in primary care offices, cardiology offices, and urgent care settings without suspected ACS to ensure inclusion of all subject profiles; however, patients undergoing testing as part of a rule-out-ACS protocol are not eligible. To ensure broad generalizability, we are using a patient-centric design and not limiting enrollment to a single care setting or single type of provider (cardiology). PROMISE reflects the care settings, patient groups, and providers who will eventually apply its results.

## **2.a Inclusion Criteria**

1. New or worsening chest-pain syndrome or equivalent symptoms suspicious for clinically significant CAD
2. No prior cardiac evaluation for this episode of symptoms
3. Planned noninvasive testing for diagnosis
4. Men age greater than or equal to 55 years and women age greater than or equal to 65 years
5. If age in men 45–54 years or women 50–64 years, then must have increased probability of CAD due to 1 or more of the following risk factors:
  - Diabetes mellitus requiring medical treatment
  - Peripheral arterial disease (PAD), defined as documented peripheral arterial stenosis greater than or equal to 50%, treated medically or invasively
  - Cerebrovascular disease (stroke), defined as documented carotid stenosis greater than or equal to 50%, treated medically or invasively
  - Ongoing tobacco use
  - Hypertension
  - Abnormal ankle-brachial index (ABI), defined as less than 0.9
  - Dyslipidemia
6. Serum creatinine less than or equal to 1.5 mg/dL within the past 90 days
7. Negative urine/serum pregnancy test for female subjects of childbearing potential

## **2.b Exclusion Criteria**

1. Diagnosed or suspected ACS requiring hospitalization or urgent or emergent testing; elevated troponin or creatine kinase-myocardial band (CK-MB);

---

outpatients who have completed a rule-out ACS protocol are eligible provided they have negative biomarkers x 2 and a nondiagnostic or normal ECG.

2. Hemodynamically or clinically unstable condition (systolic blood pressure [BP] less than 90 mm Hg, severe atrial or ventricular arrhythmias, or persistent resting chest pain felt to be ischemic despite adequate therapy)
3. Known CAD with prior clinical history of MI, PCI, coronary artery bypass graft (CABG) or any angiographic evidence of CAD greater than or equal to 50% lesion in a major epicardial vessel
4. Any invasive coronary angiography or noninvasive anatomic or functional cardiovascular test for detection of CAD, including CTA and exercise ECG, within the previous 12 months (+/- 30 days); prior resting ECG and/or resting echo do not constitute an exclusion to participation
5. Known significant congenital, valvular (greater than or equal to moderate) or cardiomyopathic process (hypertrophic cardiomyopathy or reduced systolic left ventricular [LV] function [LV ejection fraction less than 40%]) that could explain cardiac symptoms
6. Contraindication to a CTA, including, but not limited to:
  - a. Allergy to iodinated contrast agent
  - b. Pregnancy
7. Any other contraindications that would preclude performing a CTA per local site practice, such as 1 or more of the following:
  - a. Inability to receive beta blockers if heart rate is greater than 65 beats per minute
  - b. Agatston score greater than 800
  - c. Body mass index (BMI) greater than 40
  - d. Cardiac arrhythmia
8. Life expectancy less than 2 years
9. Unable to provide written informed consent or participate in long-term–follow-up

## 2.c Ethical Considerations

### ***Human Subjects' Involvement and Characteristics***

All human adult subjects who meet inclusion criteria and who do not meet any of the exclusion criteria will be considered eligible for this trial. Subjects who are within vulnerable populations will be included at the discretion of the site institutional review boards (IRBs).

## 2.d Subject Recruitment Plans and Consent Process

Diagnostic testing for the assessment of CAD symptoms is ordered by physicians of all specialties; is performed in multiple settings, including physician offices, hospital outpatient departments, and diagnostic testing facilities; and is interpreted by physicians of multiple specialties, including primary care physicians, cardiologists, and radiologists. Therefore, subjects will be recruited from multiple clinical settings, including outpatient

clinics, urgent care centers, and testing facilities. Sites that do not perform the full range of diagnostic testing, including CTA, will be paired with regional referral centers for echo, nuclear, and/or CTA testing where subjects may undergo the necessary testing. Existing clinical referral and research networks will be used to identify and enroll subjects.

Subjects will be recruited from 200 to 250 clinical sites. All potential PROMISE sites will obtain IRB/Institutional Ethics Committee (IEC) approval of the protocol and the associated consent form and any recruitment tools. Written informed consent will be obtained from each subject before to any study procedures are performed. Assessment of CAD risk will begin during screening to ensure eligibility. It will include medical history and physical exam and laboratory testing for the presence/absence of major cardiac risk factors, including BP/hypertension, diabetes, cholesterol (low-density lipoprotein [LDL], high-density lipoprotein [HDL]), smoking, family history, sedentary life style, obesity, cerebrovascular and PAD history, and ABI.

Subjects will be identified and enrolled in a step-wise process as follows:

1. All subjects being considered for outpatient noninvasive testing for the initial evaluation of symptoms suspicious for clinically significant obstructive CAD will be screened.
2. Subjects meeting inclusion criteria and not having any of the exclusion criteria will be approached to participate in the study and have the study explained to them.
3. Subjects agreeing to participate after having all their questions answered will be asked to document their agreement on the study-specific IRB-approved consent form with a signature.

## **2.e Subject Randomization**

Eligible subjects who have given written informed consent and meet all inclusion and no exclusion criteria will be randomly assigned in equal proportions (1:1) to either the anatomic or functional diagnostic testing arm of the trial. A computer-generated permuted block randomization schedule with stratification by clinical site will be used in the trial. Before randomization, the managing caregiver, site investigator, or authorized designee will be asked to indicate the functional test he or she would plan to use if the subject were randomized to the functional testing arm. This information will be tracked and used as another stratification factor in the randomization scheme to facilitate comparisons of anatomic vs. functional testing according to the type of functional test. Subject randomization will be accomplished by telephone through a centralized toll-free interactive voice response system (IVRS).

If a subject is randomized but does not undergo the planned initial diagnostic test within 30 days of randomization, that subject will still be followed and included in the intention-to-treat statistical comparisons according to his or her randomized treatment assignment.

## **2.f Risks and Benefits**

### ***Potential Risks***

Protocol-specific risks associated with the PROMISE trial are minimal. All PROMISE enrolled subjects will, by inclusion criteria, require noninvasive testing for their symptoms. Thus all subjects will have compelling medical reasons for performance of

---

the noninvasive test arm to which they are randomized. All care in PROMISE is part of routine clinical practice and, because the only intervention being performed in PROMISE is the random assignment of initial diagnostic test, safety considerations and adverse events are limited to complications arising from initial testing. Reporting of these safety events will be the responsibility of the site investigator.

### ***Drawing Blood***

Risks associated with drawing blood include momentary discomfort and/or bruising, infection, excess bleeding, clotting, or fainting.

### ***Potential Loss of Confidentiality***

In any clinical trial, there is a possible risk to subjects as to the potential loss of confidentiality. To prevent this from occurring, the Clinical Coordinating Center (CCC) and the Statistical and Data Coordinating Center (SDCC) at the Duke Clinical Research Institute (DCRI) have strict procedures in place to ensure that all study data are confidential and anonymized except as required for data collection by the Economics and Quality of Life Coordinating Center (EQOL CC) and the DCRI Outcomes and Follow-up Group (DOFG). For all data received by DCRI, subjects will be identified only by unique code numbers. The link to these codes will be maintained at the SDCC. Trial records that identify subjects will be kept secure and confidential as required by law. Federal privacy regulations provide safeguards for privacy, security, and authorized access.

If the DOFG finds that a subject has undergone diagnostic testing or a diagnostic or therapeutic procedure or has been hospitalized, the DOFG will obtain the subject's test results or discharge summary, and the EQOL CC will obtain relevant medical billing information on behalf of the trial. Once received at the SDCC, these documents will be anonymized, removing the subject's name, personal identifiers, and local physician's name and will be identified by unique study enrollment numbers.

### ***Potential Benefits***

The PROMISE trial results should improve the care of future subjects requiring diagnostic testing for suspected CAD. In addition, the trial will deliver high-quality data on radiation exposure, incidental findings, and other clinically important "side effects" of the testing strategies that will be examined in a large real-world experience.

## **D3 Diagnostic Testing**

### **3.a Approach to Diagnostic Testing**

An important goal of PROMISE is the broadest possible applicability of its results. Therefore, all commonly used tests are included in the functional testing arm, a designation that generally implies a multiplicity of approaches. This inclusiveness will facilitate enrollment by ensuring that all eligible subjects will have ready access to high-quality testing in both arms. Because the preferred type of functional test will be recorded by the IVRS before randomization, the trial subjects, each of whom has been selected by his or her managing clinician to undergo a different form of functional testing, can later be divided into 3 cohorts for prespecified subgroup analyses. In each cohort, half will be randomized to undergo that prespecified functional test, while the other half

---

will be randomized to undergo CTA, forming paired CTA-functional test subgroups for each functional test type.

We will ensure that the standard of care of testing and imaging performance and interpretation consistent with good medical practice is maintained throughout the trial by requiring that sites have expertise and qualify in all modalities, by providing recommended imaging protocols and by providing timely quality feedback and expert overreading in a subset of studies, again for all modalities.

### **3.b Description of Testing To Be Performed**

Subjects will initially be evaluated according to their physicians' specific protocols for management of subjects with an indication for nonurgent, noninvasive cardiovascular testing. Typically, the standard evaluation will include the relevant past and current medical history, a physical examination, and a resting 12-lead ECG and may include cardiac biomarkers (troponin and/or CK-MB) as well as other routinely obtained blood testing. Subjects who meet eligibility criteria will have their physicians' preferred functional tests designated as part of the stratification requirements for randomization.

#### ***Functional Testing Arm***

For subjects randomized to usual care, the preselected functional test will be performed as the initial test. This includes stress nuclear imaging, stress echo, or exercise ECG.

#### ***Anatomic Testing Arm***

In subjects randomized to the anatomic testing arm, a contrast-enhanced coronary CTA will be performed as the initial test.

#### ***Subsequent Care***

The results of all tests will be provided to the care team in the usual manner for that testing laboratory, and, depending on the results, subjects may or may not undergo medical treatment and/or additional noninvasive functional, anatomic, or invasive testing (coronary angiography), and/or coronary revascularization, at the care team's discretion. It is assumed that patient management will be additionally informed and guided by the test findings. The local physician will resume care of the subject and make all subsequent clinical decisions (e.g., need for further evaluation or admission) based upon his or her cumulative clinical assessment of the subject, including findings revealed on the noninvasive testing.

### **3.c Functional and Anatomic Testing and Cardiac Catheterization**

#### ***Equipment and Protocols***

Criteria for qualification of participating sites or referral laboratories will include use of standard equipment for usual-care testing (stress echo, stress nuclear, and exercise ECG) as defined in current practice guidelines, and greater than or equal to 64-slice MDCT technology for coronary CTA. Similarly, all test acquisition protocols will adhere to best-practice standards as defined in current national practice guidelines.

 Sites will be allowed to use their own standard acquisition protocols as long as they

---

fall within the standard-of-care guidelines. Sample protocols are provided in the Manual of Operations and Procedures (MOP).

### ***Interpretation***

All studies will be interpreted by qualified physicians who have at least ACC COCATS (Core Cardiology Training Symposium) level 2 training or equivalent. For nuclear studies, certification by the Certification Board of Nuclear Cardiology or Board Certification in nuclear medicine or radiology is also sufficient to qualify as a reader. Coronary CTA will be interpreted by physicians trained at least COCATS level 2 or equivalent, either Society of Cardiovascular Computed Tomography level 2 or the Certification Board of Computed Cardiovascular Tomography. However, because coronary CTA is a relatively new technology, and practice requirements and expertise may not have evolved to the same level as other diagnostic tests, reader qualification may include online review and evaluation of clinical cases consisting of paired coronary CTA and invasive angiography datasets.

All diagnostic tests will be interpreted and reported by diagnosticians at the sites in real time according to current guidelines to ensure timely availability of results for patient management. The diagnostic test reports will capture the major findings, including:

1. Presence and extent of CAD (CTA).
2. Resting LV function and perfusion (echo and nuclear scans) as either: normal, global dysfunction, regional dysfunction/scar, both, or not interpretable. Ejection fraction will be quantified. This information will be optionally gathered for CTA.
3. Functional capacity determined for exercise ECG, stress echo, or stress nuclear.

### **3.d Test Transfer and Storage**

Test transfer will be accomplished by transmission of paper recordings for stress ECGs and the ECG component of echo and nuclear studies. For digital images including invasive coronary angiography, transmission may be accomplished by compact disc (CD) or over the Web. For Web transmission, an image-transfer system will be deployed at the site. The data-transfer software will provide encryption, lossless compression, and transmission capabilities for the submission of deidentified data sets via the Web to the central Test Data Repository hosted by the American College of Radiology Imaging Network (ACRIN) in Philadelphia.

Upon arrival in the central data repository, datasets will be processed as needed: paper ECGs converted to PDFs; CDs uploaded; and Web images decompressed, deencrypted and imported into the central imaging database, a networked long-term image-archiving and storage system. This will ensure maximal site flexibility as well as seamless and efficient transfer of imaging data from sites into a central data repository and will allow real-time quality control and feedback.

### **3.e Quality Assurance of Diagnostic Testing**

Before beginning enrollment, eligible sites and readers will be qualified by the Diagnostic Testing Coordinating Center (DTCC) based on site and reader surveys, on successful transfer of 1 or more complete data sets with sufficient image quality and completeness for each modality, and participation in the CTA case review. Site qualification will be issued by the DTCC for each modality before subject enrollment.

---

During the study, technical quality assessment of image and test acquisition will be accomplished on all studies by central repository research technicians trained by the DTCC or by the CCC for invasive coronary angiography. This ongoing review will ensure the adequate quality and completeness of data sets (see details and definitions in the MOP) and will monitor radiation exposure in the CTA arm throughout the trial.

Expert overreading of the initial, randomized, noninvasive tests and first invasive angiogram within 60 days of randomization will be performed in approximately 10% of subjects by modality experts in the DTCC and CCC. To ensure protocol compliance early on and to account for low-accrual sites, the first 2 studies and ~10% of the remaining studies from each site will be overread in each modality. These will be selected by block randomization stratified by testing site and test modality.

In addition, to strengthen the link between site investigator reported invasive catheterization without obstructive disease and angiographic findings, a sample of invasive angiograms determined by site investigators to be without obstructive disease will undergo core lab QCA and the results compared.

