| End-of-Study Definition         | 1-year minimum follow-up of all patients, with expected 24-month average follow-up for clinical status assessment.                                                                                                                                                                                                                                                                                                                                                                                                                                                                                                                                                                                                                                                                                                                                                                                                                                                                                                                                                                                                                     |
| Number of Subjects              | Approximately 10,000 subjects will be enrolled.                                                                                                                                                                                                                                                                                                                                                                                                                                                                                                                                                                                                                                                                                                                                                                                                                                                                                                                                                                                                                                                                                        |

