The second important component of information from the diagnostic test QA activity is the quality of test interpretations. Approximately 10% of tests will be overread by the DTCC using a categorical level of coronary disease risk. The site interpretation of level of risk will be compared with the level of risk using the same scale assessed by the core lab's overread of the test, and overall summary statistics of the agreement between the site and core lab assessments will be computed. Raw proportions of agreement (perfect agreement, and agreement differing by less than or equal to 1 category of risk) will be tabulated, and Kappa statistics will be used to characterize the level of agreement. The Kappa statistics are "chance corrected" (i.e., adjusted for agreement due to chance), and both unweighted and weighted Kappa statistics will be used in these analyses since more substantial disagreements in the assessment of risk for a given subject would be more serious than small disagreements. These agreement statistics will then be compared across the different testing modalities to determine whether the level of agreement between the site readings and the core lab readings varies with the type of test.

Another important component of information to characterize data quality for the secondary endpoints that involve non-obstructive CAD will be the review of selected

---

coronary angiograms to determine the degree to which site-reported assessments of non-obstructive coronary disease are concordant with carefully-performed core lab QCA. The same type of agreement statistics as described above, including raw proportions of agreement and chance-corrected Kappa statistics, will be used to describe and characterize the accuracy of the site-reported assessments of non-obstructive CAD.

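### The protocol's over-read rule must give more than the stated 10%, and the pooled agreement statistics lean toward each site's first two studies

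*Supplement*

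**What the plan says.** The latest protocol (Amendment 2) gives the size of the over-read sample in two places. In D3 3.e, expert over-reading "will be performed in approximately 10% of subjects by modality experts in the DTCC and CCC". In F2 2.c, "Approximately 10% of tests will be overread by the DTCC using a categorical level of coronary disease risk".

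Section 3.e also gives the rule that generates the sample: "the first 2 studies and ~10% of the remaining studies from each site will be overread in each modality". On the method of selection it adds: "These will be selected by block randomization stratified by testing site and test modality". The stated purpose is early protocol compliance and coverage of sites that enrol few subjects.

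Section 2.c then plans raw proportions of agreement between site and core lab, with unweighted and weighted Kappa, and compares these across test types. The weights there reflect how far apart two readings are, not how likely a study was to be selected. The SAP does not describe the over-read sample or its analysis.

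**The concern.** The percentage and the rule stand next to each other in 3.e and cannot both hold. Ten per cent of the remainder is already close to 10% of the total, and every first-two study comes on top. The likely cause is visible in the Amendment 2 table of revisions, where the over-read percentage in 2.c goes from about 20% to about 10%. Version 1.0 and Amendment 1 have the same rule with about 20%, which lies within the range that the rule produces. The rule was not changed with the percentage.

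Two things follow. The expected core-lab workload is understated. And the sample described in 2.c is not a simple random tenth: first-two studies enter with certainty, later studies with probability about 0.1. An unadjusted agreement figure therefore gives early studies far more weight than they have among all tests, and the imbalance is largest for modalities with few tests per site. If agreement changes as a site gains experience, a difference in Kappa between modalities could reflect the share of early studies rather than the test.

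**Working it through.** **Inputs**

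- N = 10,000 initial tests, one per subject: "Approximately 10,000 subjects will be enrolled" (Synopsis A1).
- S = number of testing sites. The synopsis gives about 220 sites. Section D2 2.d says "Subjects will be recruited from 200 to 250 clinical sites". These are enrolling sites. Section 2.d also pairs sites lacking a modality with regional referral centers, so testing sites may be fewer. Their number is not given.
- M = modalities in use per site. There are four noninvasive modalities: CTA, and for the functional arm, "This includes stress nuclear imaging, stress echo, or exercise ECG". Sites must qualify in all of them, but the number each uses is not stated. I assume 2 to 4.

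**Formula**

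First-two studies: F = 2 × S × M. Total over-read: T = F + 0.10 × (N − F) = 0.10 × N + 1.8 × S × M. The excess over 10% is 1.8 × S × M / N, which is always positive.

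**Can the stated figure be reproduced?** The plan's 10% means 1,000 reads. Even 11% (1,100 reads) requires S × M ≤ 100 / 1.8, about 55 site-modality cells. At 220 sites with 2 to 4 modalities there are 440 to 880 cells. The figure does not reproduce.

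**Results**

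| Testing sites | Modalities per site | First-two | Total over-read | Share of tests | First-two share of over-reads |
|---|---|---|---|---|---|
| 220 | 2 | 880 | 1,792 | 17.9% | 49% |
| 220 | 3 | 1,320 | 2,188 | 21.9% | 60% |
| 220 | 4 | 1,760 | 2,584 | 25.8% | 68% |
| 200 | 2 | 800 | 1,720 | 17.2% | 47% |
| 250 | 4 | 2,000 | 2,800 | 28.0% | 71% |
| 100 | 2 | 400 | 1,360 | 13.6% | 29% |
| 150 | 4 | 1,200 | 2,080 | 20.8% | 58% |

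If the first two are counted per site and not per modality, 220 sites give 440 + 956 = 1,396 reads, or 14.0%, with a first-two share of 31.5%. A simulation at 220 sites with uneven accrual, and with cells of fewer than two tests capped, gave 18.7-24.8% and a first-two share of 52-66%. First invasive angiograms, which 3.e also includes, are left out because their number is not given.

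**How the imbalance can differ by modality.** As an illustration, take 5,000 CTAs and split the 5,000 functional tests by the claims mix in C5 (61% nuclear, 18% echo, 21% exercise ECG), with all four modalities at 220 sites. Each modality then has 440 first-two studies.

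- CTA: 440 + 0.1 × 4,560 = 896 reads; first-two share 49%.
- Nuclear: 440 + 0.1 × 2,610 = 701; 63%.
- Exercise ECG: 440 + 0.1 × 610 = 501; 88%.
- Echo: 440 + 0.1 × 460 = 486; 91%.

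**What this could do to an agreement figure.** The documents give no agreement rates, so assume 70% for first-two studies and 85% for later ones. At 220 sites with two modalities, the pooled sample shows 0.491 × 0.70 + 0.509 × 0.85 = 77.6%. Over all tests, of which 8.8% are first-two, agreement is 83.7%. With four modalities the figures are 74.8% and 82.4%. If early and later agreement are equal, the distortion is zero.

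**The case against.** Oversampling early studies is deliberate and sensible for monitoring, and 3.e says why it is done. That stands: the design of the sample is not at fault. The mismatch lies between the rule and the percentage, and the analysis in 2.c makes no allowance for the rule.

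The size depends on counts that the documents do not give. That also stands. Someone might take 18-26% as a fact about this trial. It is conditional on about 220 testing sites using two to four modalities, and pooling at referral centers lowers it to about 14-21%. Every one of these readings still exceeds 10%.

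A reader might infer that the pooled statistics describe start-up performance only. They do not. They are a mixture in which later studies make up about half at 220 sites with two modalities, and about 70% with 100 testing sites. The mixture misleads only if early and later agreement differ. The documents give no evidence either way, and readers are qualified before enrolment.

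A reader might also infer that these agreement statistics are meant to help interpret the comparison of the randomized arms. The sentence in 2.c to that effect concerns technical image quality, a separate component that does not use the over-read sample. The stated use of over-read agreement is to see whether it varies by test type, and the section on diagnostic accuracy lists such concordance among strictly supplementary analyses.

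**Conclusion.** The point holds as a minor inconsistency with a limited analytic consequence. The figure of about 10% in D3 3.e and F2 2.c cannot be met by the rule in 3.e under any realistic reading. The expected fraction is about 18-26% with some 220 testing sites and two to four modalities each, and about 14-21% with 100-150 testing sites. First-two studies form roughly 30-70% of the over-read sample. At 220 sites that is 792 to 1,584 reads more than the stated 1,000.

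Pooled agreement and Kappa therefore lean heavily toward early studies, to a degree that can differ by modality. This can confound the planned comparison across modalities if early and later agreement differ, which is unknown. No primary or secondary endpoint, analysis population or error rate is affected.

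**What to change.** 1. In 3.e and 2.c, replace the 10% with the fraction that the rule implies, and state the number of testing sites and modalities on which it rests. Changing the rule would achieve little. Amendment 2 is dated April 30, 2013, and the SAP has randomization starting in July 2010 and lasting about 36 months, so most first-two studies had probably already been selected.
2. In 2.c, report agreement and Kappa separately for first-two and later studies, by modality.
3. Base any overall or cross-modality figure on the later, randomly selected studies, or on inverse-selection-probability weights (1 for first-two, about 10 for later). Name these sampling weights so that they are not confused with the disagreement-weighted Kappa already planned. The weighted figure describes agreement over all tests done. A low-volume modality still carries more early studies in it (440 of 900 echo tests against 440 of 5,000 CTAs in the illustration), so the separate figures from step 2 should be read first when modalities are compared.

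The cost is wording, one selection indicator in the data set, and some precision. The effective sample of the weighted figure is (Σw)² / Σw². With two modalities at 220 sites it is 10,000² / (880 + 100 × 912) = 1,086 of 1,792 reads. With four it is 10,000² / (1,760 + 100 × 824) = 1,188 of 2,584. Later-only figures for the rarer modalities would be thin, about 46 echo and 61 exercise ECG reads in the illustration. No additional reads are needed.
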